
#### 2.5.2. Secondary Outcomes

Self-reported school, training or work experience, performance and attendance will be measured using 5 ad-hoc items asking for perceived caring-related difficulties in education/training/work (e.g., “I miss school/training/work”; “It is difficult for me to perform well at school/training/work”; “While at school/training/work, I worry about the person I care for”). Items are rated on a 5-point frequency scale (from never to always). Three ad-hoc items (5-point scale ranging from yes, absolutely to absolutely not) will assess likeliness to complete and continue education/training compared to before participation.

#### 2.5.3. Control Variables

Caring activities will be measured using the multidimensional assessment of caring activities [105] (18 items, 3-point scale ranging from never to a lot of the time), which asks for time spent on domestic tasks, household management, personal care, emotional care, sibling care and financial/practical care. To assess the overall amount of caring, 2 questions taken from the “Manual for Measures of Caring Activities and Outcomes for Children and Young People” [110] will be used that ask for the number of hours of caring per week for a typical day during the week and at the weekend. To assess likes and dislikes about caring, 4 open-ended questions based on the Joseph et al. manual [110] will be used that ask AYCs, which one of their caring jobs they like the most, dislike the most, that gratifies them the most or upsets them the most. Three multiple-choice ad-hoc questions will assess formal support or services that AYCs and someone in their family receive (i.e., care package, equipment, transportation assistance, benefits and allowances), and whether school staff, other family members and friends have been trusted or know about their caring situation.

#### 2.5.4. Post-Intervention Self-Assessment

At both T1 and T2, AYCs allocated to the ME-WE intervention group will be asked to complete an adaptation of the post intervention self-assessment by Joseph et al. [110]. This tool includes 7 dichotomous (Yes/No) items on the ME-WE intervention (e.g., “I enjoyed most of the activities”), 10 items (3-point scale ranging from more often than before the intervention to less often than before the intervention) about changes related to participation (e.g., “I feel able to choose the level of care I provide”) and 5 open-ended questions (see next section).

#### 2.5.5. Process Evaluation Outcomes

A number of process evaluation outcomes will be monitored, following Linnan and Steckler [111]. Indicators of feasibility will include the proportion of eligible AYCs who will participate in the trial, the proportion of AYCs in the intervention group who will attend ≥70% of intervention sessions, and the proportion of AYCs who will be lost to follow-up. These feasibility indicators will be assessed using attendance lists (for the intervention group) and completion of assessment questionnaires (for the control group). To assess intervention acceptability, 5 open-ended questions included in the post-intervention self-assessment [110] will ask AYCs for their perceptions about the support they received from the intervention, what changed for them and for their caring role because of participating in the intervention and what they did not like about the intervention. For fidelity, a semistructured questionnaire will be completed by cofacilitators following each intervention session to evaluate whether the ME-WE intervention was delivered as planned.

### 2.6. Piloting of the ME-WE Intervention and Assessment Questionnaires

Between March and May 2019, a small pilot study was carried out in Italy and the Netherlands with groups of 5 and 4 AYCs, respectively, to assess the suitability of the ME-WE intervention for our target group. Participants’ feedbacks were collected in group discussions with questions related to their satisfaction with intervention overall arrangement, timing and contents, and to individual experiences during session and home activities. Altogether, timing and contents were rated favorably, and intervention activities and exercises were well received among AYCs. Only minor adjustments were proposed, such as the need for introducing physical materials used (e.g., cards) and emphasizing that there are no correct or incorrect interpretations of the stimuli proposed in the session exercises, and more clearly explaining home activities and their voluntary nature. Proposed adjustments were subsequently implemented. In May 2019, the assessment questionnaire was piloted with two groups of AYCs from Italy (*n* = 4) and the United Kingdom (*n* = 5) to evaluate comprehensibility, acceptability and completion time. In general, the tool was deemed comprehensive and easy to understand and respond. Mean questionnaire completion time was 20 min. Altogether, the pilot studies provided useful information on practicality and suitability of the study materials.

### 2.7. Sample Size Calculation

For the primary outcome variables, a moderate effect size (*f* = 0.25) was pursued based on previous evidence in RCTs using ACT-based interventions [56,84,112]. A minimum group size of 24 AYCs was established based on power analyses with a power of 80% and an α-error probability of 5%. However, in the case of cluster RCTs, an effective sample size is in fact lower than that suggested by the actual number of participants due to observations on participants in the same cluster tending to be correlated [62]. Thus, initial sample size estimation (performed as if randomization occurred at the individual level) was corrected taking into account randomization occurring at the cluster level. For each country, an average cluster size was estimated using the formula for sample size determination in a finite population [113] and assuming the prevalence rate of AYCs in the population of adolescents aged 15–17 in that country. Based on available data, the estimated prevalence rate of YCs is about 3% in Italy [114], 7% in Sweden [115], about 8% in Switzerland [3], 6% in the Netherlands [116] and in the United Kingdom approximately 7% of all children are engaged in a high amount of caring and 3% in a very high amount [117], while no estimation is available yet for Slovenia. As Italy and Slovenia have both been classified as countries at the initial stage of awareness concerning AYCs [118], the Italian prevalence rate was also applied in the Slovenian sample size calculation. A design effect was then calculated using the average cluster size and an assumed intracluster correlation of 0.05. This design effect was multiplied by the initial sample size to obtain a sample size corrected for the cluster-based design, which was further increased by 20% to compensate for attrition. The minimum total sample sizes obtained from this procedure were as follows: 80 AYCs (40 AYCs in the intervention and 40 AYCs in the waitlist group) in Italy and Sweden, 76 AYCs (38 AYCs in the intervention and 38 AYCs in the waitlist group) in Slovenia, 102 AYCs (51 AYCs in the intervention and 51 AYCs in the waitlist group) in Switzerland, 112 AYCs in the Netherlands (56 AYCs in the intervention and 56 AYCs in the waitlist group) and 142 AYCs (71 AYCs in the intervention and 71 AYCs in the waitlist group) in the United Kingdom.

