## 2. Original Study Protocol Methods

### 2.1. Study Design

This study is a two-armed, parallel group cluster RCT that will be executed in six European countries (Italy, Slovenia, Sweden, Switzerland, the Netherlands and United Kingdom). Cluster randomization is used to minimize contamination between intervention and control arms [61]. Indeed, if randomization were performed at the individual participant level, there would be a risk for exchange of information between AYCs within the same cluster. Clusters will consist of AYCs attending the same school (in Slovenia, Sweden and Switzerland) or living in the same geographical area (i.e., neighborhood or post-code area) (in Italy, the Netherlands and the United Kingdom). Clusters will be randomly assigned to either the ME-WE intervention or the waitlist control (1:1 allocation ratio), so that all eligible participants from the same school or geographical area are in the same study arm. Randomization will be conducted by a research member who is neither involved in the recruitment nor in the intervention delivery, using an online number generator. To achieve a certain degree of blinding, both schools and community-based service organizations (for geographical area clusters) and participating AYCs will be informed that the study aims to investigate the effects of different support strategies on AYCs’ well-being. They will not be told which condition they have been allocated to, nor will they be offered detailed information about the respective other trial arm during the study. Outcomes will be measured at the individual level. Both the ME-WE intervention and the waitlist control group will be assessed at baseline (T0), immediately post-intervention for the ME-WE intervention group or after 7 weeks for the waitlist control group (T1), and at a 3 months follow-up (T2). Participant-reported outcome measures will be used. Trial data analysts will be blinded to group allocation. After the 3 months follow-up the waitlist control group will receive the same program as the intervention group. The consolidated standard of reporting trials (CONSORT) 2010 statement extended to cluster trials is followed in this study [62]. The research flow diagram is presented in Figure 1. This protocol is based on the SPIRIT (standard protocol items: recommendations for interventional trials) guidelines [63] and has been registered at clinicaltrials.gov (accessed on 22 September 2019, trial registration number: NCT04114864).

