### 2.8. Statistical Analyses

Statistical analyses will be performed at both national and cross-national levels. Data will be analyzed using intention-to-treat principles [119] and adjusted for cluster effect [62]. Baseline characteristics will be preliminarily compared to check equivalence between study groups using analysis of variance (ANOVA) and *χ*^2^ tests. To answer primary and secondary research questions, differences in primary and secondary outcomes between the study arms from T0 through T1 and T2 will be tested using linear mixed effect models. These analyses will be based on individual participant-level data, allowing for clustering between AYCs within the same school or geographical area [62,120]. Models will include the fixed effects of study arm, country and delivery approach, time and their interaction effects. The cluster will be considered as a random effect. Models will be adjusted for characteristics that are unbalanced between study arms and significantly associated with the outcome measures. In case of violations of assumptions underlying planned analyses (e.g., equal variance and normal distribution of residuals) appropriate mathematical transformations of raw scores (e.g., logarithmic scale) or robust estimation methods will be applied [121]. Interpretation of results will be based on both statistical significance (*p* < 0.05, two-tailed) and measures of effect size [122]. We will also summarize post-intervention self-assessment and process evaluation measures. Analysis of qualitative data in national languages (for control variables likes and dislikes about caring and for intervention acceptability) will be performed using content analysis [123].

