### 3.5. Sample Size Calculation Amendments

The minimum required sample size was revised for Sweden and Switzerland, since randomization in these countries will occur at the individual participant level. A minimum group size of 24 AYCs was established based on power analyses with a medium effect size, a power of 80% and an α-error probability of 5%. Compensating for attrition (20%), a minimum total sample size of 58 AYCs (29 AYCs in the intervention and 29 AYCs in the waitlist group) will be required in Sweden and Switzerland.

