## 4. Trial Status

The recruitment of participants started in May 2019. Randomization began in September 2019, and the first baseline assessment was completed on 24 October 2019. Before COVID-19-related amendments (April 2020), a total of 98 AYCs was recruited. The trial is currently ongoing. Preliminary data available from Italy (*n* = 22, October 2019–March 2020) indicated feasibility of the ME-WE trial and acceptability of the ME-WE intervention. The proportion of eligible AYCs (screened between May and September 2019) who participated in the trial was 84%. Seventy-three percent of AYCs in the intervention group attended at least 70% of intervention sessions. Twenty-eight percent of all participants were lost to follow-up. Responses of AYCs in the intervention group to the post intervention self-assessment indicated that participants had a clearer vision of their thoughts, took better care of themselves and were generally satisfied with and enjoyed the intervention.

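### The 20% attrition uplift leaves slightly fewer than the required 24 per arm, and 24 per arm does not follow from the stated inputs for a moderate between-arm difference

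*Protocol article*

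**What the plan says.** Section 2.7 sets the target for the primary outcomes: "a moderate effect size (*f* = 0.25) was pursued". It continues: "A minimum group size of 24 AYCs was established based on power analyses with a power of 80% and an α-error probability of 5" per cent. It names no test, contrast, number of visits or correlation between visits. The 24 is multiplied by a design effect using "an assumed intracluster correlation of 0.05", "which was further increased by 20% to compensate for attrition". The resulting minimum per arm is 40 in Italy, 38 in Slovenia, 56 in the Netherlands and 71 in the United Kingdom.

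Section 3.5 replaces the Swedish and Swiss sizes after the move to individual randomization. It starts again from 24 per group for a medium effect: "Compensating for attrition (20%), a minimum total sample size of 58 AYCs", that is 29 per arm.

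Section 2.8 plans analyses for each country as well as across countries, using linear mixed models over T0, T1 and T2 and judged by "statistical significance (*p* < 0.05, two-tailed") together with effect sizes. Section 3.6 plans a mixed ANOVA for Sweden and Switzerland. Section 4 reports on 22 Italian participants: "Twenty-eight percent of all participants were lost to follow-up".

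**The concern.** Every national sample size is built on the 24. A reader will take f = 0.25, called moderate, as half a standard deviation between two arms, and will take each country to have 80% power for it. If the 24 comes from a different effect scale, a non-significant national result could be read as evidence against a moderate benefit that the country's sample would often miss.

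Separately, an allowance for 20% loss should leave the required number after 20% are lost. Adding 20% does not do that.

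**Working it through.** **Attrition: the plan's figure first**

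Section 3.5: 24 × 1.2 = 28.8, rounded to 29 per arm, 58 in total. This matches the plan, so the uplift is a multiplication by 1.2.

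- After 20% loss: 29 × 0.8 = 23.2, below 24.
- Uplift that leaves 24: 24/(1 − 0.20) = 30 per arm, 60 in total.
- In general, 1.2 × 0.8 = 0.96, so 4% of the required number is missing.

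For the cluster countries, the number required before attrition is the stated size divided by 1.2. The article gives no cluster sizes, so this is solved back from the totals and is not an independent check on the design effect.

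| Country | Stated per arm | Required (÷ 1.2) | Left after 20% loss | Required ÷ 0.8 |
|---|---|---|---|---|
| Italy | 40 | 33.3 | 32.0 | 42 |
| Slovenia | 38 | 31.7 | 30.4 | 40 |
| Netherlands | 56 | 46.7 | 44.8 | 59 |
| United Kingdom | 71 | 59.2 | 56.8 | 74 |

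In effective terms each keeps 24 × 0.96 = 23.04 per arm. In the calculation that reproduces 24 (below), going from 24 to 23 per arm lowers power from 80.2% to 78.3%.

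**Power: where 24 comes from**

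Inputs from the article: f = 0.25, 80% power, 5% alpha, two-sided (stated for the analysis, not for the sample size), "1:1 allocation ratio", three visits. The correlation ρ between visits is not given; every value below is an assumption.

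1. *Two arms, one visit.* d = 2f = 0.5. By the noncentral t distribution, 64 per arm gives 80.1% power and 24 per arm gives 39.6%.

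2. *Arm-by-time interaction, three visits.* Noncentral F with λ = f² × N × m/(1 − ρ), on 2 and 2(N − 2) degrees of freedom. With N = 48, m = 3 and ρ = 0.1, λ = 0.0625 × 48 × 3/0.9 = 10.0 and power is 80.2%. Here 48 is the smallest total that reaches 80%, so this reproduces 24 per arm. With f held at 0.25, power is 97% at ρ = 0.5.

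3. *What f = 0.25 means on that scale.* Suppose the arms are equal at T0 and differ by d SD at both T1 and T2. The between-arm gaps are 0, d, d with mean 2d/3. The interaction deviations per cell are ±(−d/3, d/6, d/6). Their mean square over six cells is 2(d²/9 + d²/36 + d²/36)/6 = d²/18, so f = d/√18. Then f = 0.25 means d = 0.25 × 4.243 = 1.06 SD.

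4. *Power of that interaction for d = 0.5.* f = 0.5/4.243 = 0.118 and N = 48:

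| Assumed ρ | λ | Power |
|---|---|---|
| 0.1 | 2.22 | 24% |
| 0.5 | 4.00 | 40% |
| 0.7 | 6.67 | 62% |
| 0.8 | 10.0 | 80% |

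5. *Detectable gap at 80% power.* Setting λ = 10 gives d²/18 × 144/(1 − ρ) = 10, so d = √(1.25(1 − ρ)). This is 1.06, 0.79, 0.61 and 0.50 SD at ρ = 0.1, 0.5, 0.7 and 0.8.

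6. *A more efficient contrast.* The mean of T1 and T2 adjusted for T0 has variance factor (1 + ρ)/2 − ρ², which is 0.50 at ρ = 0.5 and 0.36 at ρ = 0.7. For d = 0.5 and 24 per arm, power is about 67% and 81%.

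**The case against.** The strongest reply is that 24 is not a miscalculation. The planned analyses are repeated-measures models over three visits, and an interaction f of 0.25 yields exactly 24 per arm at ρ = 0.1 and more than 80% power at higher ρ. That stands. A reader might infer that 24 is simply wrong, or that each country really has only 40% power. The documents support neither: the 40% belongs to an unadjusted single-visit t-test that Sections 2.8 and 3.6 do not plan, and some analyses do reach 80% for 0.5 SD when ρ is high. The reply does not rescue the label "moderate", because under the pattern in the working, the same f that gives 24 is about 1.06 SD between arms.

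It can also be said that an article may leave the test and correlation to a fuller document. True, and their absence alone would be no finding. But the article itself states the effect size, the power and the resulting number, and for a moderate two-arm difference these do not fit together.

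On attrition, the error is small. In the cluster countries more than 24 people per arm remain, and only the effective number falls to about 23. Participants who miss T2 still contribute T0 and T1 to a mixed model, so multiplying by 0.8 somewhat overstates the lost information there.

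The 28% loss might be read as proof that 20% is untenable. It is preliminary, from one country and 22 people. About 6 of 22 has a 95% interval of roughly 11% to 50%, which includes 20%, and the data predate the move to online delivery.

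**Conclusion.** The attrition factor is wrong as written. At the planned 20% loss every current size retains 96% of its target, a minor matter worth about 2 points of power.

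The power statement needs correction and is of moderate importance. The 24 per arm does not give 80% power for a 0.5 SD difference between arms under most readings; it does so only at fairly high correlations (interaction near 0.8, T0-adjusted mean of T1 and T2 near 0.7). These figures rest on assumed correlations, on 24 effective participants per arm and, for the interaction, on equal arms at T0 with a constant gap afterwards. What is established is a mismatch between the stated effect and the stated number, not an arithmetic error in the 24.

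**What to change.** In Sections 2.7 and 3.5:

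- Replace the uplift with n/(1 − loss). This gives 30 per arm (60 in total) in each of Sweden and Switzerland, and about 42, 40, 59 and 74 per arm in Italy, Slovenia, the Netherlands and the United Kingdom. Alternatively, keep the present sizes and say that about 23 effective per arm remain, with slightly lower power.
- State the test, contrast and between-visit correlation that produced 24.
- Replace the claim of 80% power for a moderate effect in each country with the detectable difference in SD units for the planned repeated-measures analysis, over a range of correlations.
- Show 28% loss only as a sensitivity figure, labelled preliminary (Italy, n = 22): 29 × 0.72 = 20.9 per arm.

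Cost: keeping the sizes needs no extra participants, only less favourable stated figures. Correcting the uplift raises the minimum totals by 2 in each of Sweden and Switzerland, 4 in each of Italy and Slovenia, and 6 in each of the Netherlands and the United Kingdom, 24 in all.

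### Section 3.5: 24 per arm is multiplied by 1.2 to cover 20% attrition, but a 20% loss from the resulting 29 leaves 23.2, below the stated minimum of 24.

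*Protocol article*

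**What the plan says.** Section 2.7 of the protocol article starts from an effect size: "For the primary outcome variables, a moderate effect size (*f* = 0.25) was pursued". It then gives the number per arm: "A minimum group size of 24 AYCs was established based on power analyses with a power of 80% and an α-error probability of 5" per cent. For the cluster-randomised design this number is multiplied by a design effect ("A design effect was then calculated using the average cluster size and an assumed intracluster correlation of 0.05"), and the result "which was further increased by 20% to compensate for attrition". Section 2.7 gives 20% as the size of the increase and does not separately name an expected attrition rate.

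Section 3.5 revises the size for Sweden and Switzerland, which moved to individual randomisation. It restates 24 per arm at 80% power, applies no design effect, and concludes: "Compensating for attrition (20%), a minimum total sample size of 58 AYCs (29 AYCs in the intervention and 29 AYCs in the waitlist group"). Here 20% is attached to attrition itself.

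**The concern.** Increasing a number by 20% and then losing 20% of the result does not restore the starting number, because the loss is taken from the larger figure. To keep n after losing a fraction d, one enrols n/(1 − d), not n × (1 + d). If section 3.5 used the second form, its three statements (a minimum of 24 per arm, compensation for 20% attrition, a minimum total of 58) cannot all be true.

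At stake is whether the two individually randomised countries keep the number that their own power calculation asks for, at exactly the attrition planned for. Section 2.8 plans analyses at national level, so each national minimum has to stand by itself. Section 3.6 assigns these two countries a mixed ANOVA over T0, T1 and T2, which in its usual form uses only participants with complete data. The number of completers is therefore the relevant count.

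**Working it through.** **Inputs.** Required per arm: 24 (sections 2.7 and 3.5). Attrition: 20% (section 3.5). Allocation: "1:1 allocation ratio" (section 2.1). Printed size: 29 per arm, 58 in total (section 3.5).

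**Reproducing the printed figure.**
- n × (1 + d) = 24 × 1.2 = 28.8, rounded up to 29 per arm and 58 in total. This matches.
- n/(1 − d) = 24/0.8 = 30 per arm and 60 in total. This does not match.

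**What 29 per arm covers.**
- After 20% loss: 29 × 0.8 = 23.2, below 24.
- Largest loss that still leaves 24: 1 − 24/29 = 17.2%. In whole people, five losses leave 24 and six leave 23.
- Before rounding, a factor of 1.2 covers 1 − 1/1.2 = 16.7%. A 20% loss leaves 1.2 × 0.8 = 0.96 of the requirement.

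**Power at 23.2 per arm.** The article does not state the test or the correlation between repeated measures behind the figure of 24, so this is conditional.
- Taking 24 per arm as exactly 80% power, two-sided 5%, normal approximation: (1.960 + 0.842) × √(23.2/24) = 2.755; 2.755 − 1.960 = 0.795, which gives 78.7%. The noncentral t or F calculation gives 78.5 to 78.6%.
- As a check, assume an arm-by-time interaction with f = 0.25, three time points and a correlation of 0.1. Power is 80.2% at 24 per arm and 78.7% at 23.2.
- With correlations of 0, 0.2 and 0.3 instead, power moves from 75.6 to 74.0%, from 84.9 to 83.5%, and from 89.5 to 88.4%. The drop is 1.1 to 1.6 points throughout.

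**The cluster-randomised countries (section 2.7).** The form is 24 × [1 + (m − 1) × 0.05] × 1.2, where the average cluster size m is not printed. Two steps show why the result above cannot simply be carried over.

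1. *Totals.* Dividing a printed size by 1.2 and then by 0.8 treats a rounded figure as exact. Applied to 29, it gives 30.2, rounded up to 31, although the right answer is known to be 30. If the printed sizes were rounded up per arm, the n/0.8 sizes would be 41 or 42 (Italy), 39 or 40 (Slovenia), 58 or 59 (Netherlands) and 73 or 74 (United Kingdom). With 60 each for Sweden and Switzerland, the six-country total would lie between 542 and 550. Other rounding rules shift these ranges.
2. *Power.* Take Italy, from "80 AYCs (40 AYCs in the intervention and 40 AYCs in the waitlist group) in Italy and Sweden". Solving back, 40/1.2 = 33.3; 33.3/24 = 1.389; m = 1 + 0.389/0.05 ≈ 8.8. A 20% loss leaves 32 per arm. If it thins clusters evenly, m falls to about 7.0, the design effect to about 1.30, and the effective size is 32/1.30 ≈ 24.6, above 24. For the United Kingdom ("142 AYCs (71 AYCs in the intervention and 71 AYCs in the waitlist group) in the United Kingdom"), m ≈ 30.3 falls to about 24.2, the design effect to about 2.16, and 56.8/2.16 ≈ 26.3. If whole clusters are lost instead, the design effect is unchanged and the effective size is 0.96 × 24 ≈ 23.0.

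**The case against.** The strongest reply is that this concerns one participant per arm and about 1.5 points of power, set against an assumed effect size and a figure of 24 whose test is not stated. Preliminary Italian data in section 4 (n = 22) show 28% lost to follow-up, which matters far more: at that rate 29 would leave 20.9. All of this stands. It limits the importance of the point without removing the contradiction, and the Italian rate is a separate question.

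It can also be said that 80% power is attached to 24 per arm and not to completers, and that participants with partial follow-up still contribute. This has force for the cluster-randomised countries, where section 2.8 plans linear mixed models under intention to treat. It has less force for Sweden and Switzerland, where section 3.6 specifies a mixed ANOVA. An allowance said to compensate for attrition has no purpose unless the required number remains afterwards.

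A reader might infer that every national minimum is too small and that 80% power is missed in all six countries. The article does not support that. Section 2.7 gives 20% only as the increase, the cluster sizes are not printed, and a fall in the design effect can offset the lost headcount.

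**Conclusion.** The point holds for Sweden and Switzerland. By its own inputs, section 3.5 prints a size that covers at most 17.2% attrition, not 20%. The shortfall is one participant per arm (29 against 30) in each country. If 24 per arm gives 80% power and participants lost to follow-up contribute nothing, power at 20% loss is just under 79%.

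For section 2.7 the conclusion is narrower. A 20% increase covers a headcount loss of about 16.7% before rounding. No corrected total and no loss of power should be claimed for Italy, Slovenia, the Netherlands or the United Kingdom. It is a minor numerical correction, but it affects a current, amended sample size.

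**What to change.** In section 3.5, do one of the following:
- keep 58 and state that it allows for about 17% attrition, with power just under 79% at 20% loss if 24 per arm gives 80%; or
- print 30 per arm, 60 in total, from 24/0.8.

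In section 2.7, add that a 20% increase covers about 16.7% loss of headcount before rounding. If the sponsor intends 20% attrition to be covered there too, it should recompute from its own unrounded cluster-corrected sizes, not from the printed totals.

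The first option costs a sentence and changes no enrolment. The second adds two participants in each of Sweden and Switzerland.
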